### Sources of data collection

#### Quantitative data

Population within project sitesRoutine data from the selected sites(facilities)Baseline survey

#### Qualitative

ToolsBaseline surveyObservationsProject information

### Control group – Minimizing bias and contamination

To minimize bias and contamination, the intervention sites will be selected purposely from the nine county and sub- county hospitals. The sites selected will include the two facilities that have some level of neonatal facilities to ensure that the intervention sites and the control sites have distinct features separating the two.

We will measure the utilization of services in the selected facilities at baseline, mid-term and end-line levels.

To determine utilization of neonatal services, we will collect data directly from the source through a data abstraction form in the nine health facilities throughout the project period. Further, the community health workers and volunteers will also provide information of the number of cases they refer to specific facilities. Cases that fail to arrive at the health facilities will also be captured and the data from the facilities and the community health workers will be cleaned, cross checked and analyzed to provide required results for utilization of neonatal services.

Quality of care will be determined through observations of service provision by clinicians, as well as checking use of neonatal equipment and the severity of conditions managed by the health providers in the units.

### Sample size determination

#### Selection of community members (newborn mothers)

Bungoma County, the area targeted by community sensitization will be source area for target newborn caregivers/newborn mothers who will be simple randomly selected to participate in the survey. Statistical methods for determining sample size will be employed to ensure the correct sample size is picked to avoid biases and ensure the outcomes are valid. There are approximately 29,845 births in Bungoma County per annum [16]. This number will be split twice for control and intervention group. The study will allow a margin of error of 5% at confidence level of 95% to obtain the correct sample size for the study. It is also expected that at least one of the variables of interest (e.g., knowledge of 3 danger signs in neonates) will be 50% among the respondents. Using the formula:$$ x=Z{\left({}^c{/}_{100}\right)}^2r\left(100-r\right) $$$$ n{=}^{N\ x}{{/_{\Big(\left(N-1\right)E}}^2}_{+x\Big)} $$$$ E=\mathrm{Sqrt}\left[{}^{\left(N-n\right)x}{/}_{n\left(N-1\right)}\right] $$where *N* is the population size, *r* is the fraction of responses that we are interested in, and *Z*(*c*/100) is the critical value for the confidence level *c*, we get 375 as our ideal sample size in the control and intervention areas (i.e., four data collectors in each area conducting 8 surveys daily for 12 working days each). See Additional file 1.

**Table 1 Tab1:** Outcomes and objectives

Outcomes	• Increased access and utilization of quality neonatal care services. • Health system management strengthened to deliver quality neonatal health services.
Objectives	i) To setup 7 differentiated neonatal special care units in 7 sub-county hospitals in Bungoma. ii) To train 90 selected health workers (nurses and clinicians) based in 9 sub county hospitals in neonatal care to be able to diagnose and manage common new-born problems and make timely referral when appropriate. iii) Establishing a tele-health platform that will ease diagnostic and new-born clinical care consultant support iv) Re-packaging and distribution of best-practice clinical guidelines into user friendly formats. v) Develop a mobile phone based follow up system for all new-borns for early detection of neonatal problems and initiation of appropriate action.

#### Selection of hospitals for the study

There are 177 health facilities in Bungoma County of which 12 are hospitals and the rest are health centers, dispensaries and clinics. In this study, nine high volume health facilities will be selected to participate in the study. Five Facilities will be intervention sites while four health facilities will be the control sites. The intervention sites will be selected purposely from the nine project facilities.

#### Selection of participants for the clinical observations of neonatal services

The sample size calculation is based on net change in the proportion of neonates who present with complications in health facilities. From the County HMIS data, it is estimated that a significant proportion of babies born with complications are missed out or only a few of them present to health facilities. In Bungoma County, currently only 21% present in health facilities. Through the Newborn collaborative support project, we seek to increase this by 50%, (21 to 32%). Given that births are 29,845 [16] and current situation is 21% presenting in health facilities we get a population of 6268 neonates. This means we get a sample size of 125 neonates for intervention and 125 for control group. Data collection tools such as questionnaires will be administered randomly amongst the selected cases. See Additional file 2.

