### Study questions

To what extent does increase in community knowledge on neonatal complications and availability of quality services affect mothers/new born caregivers utilization of hospital services in Bungoma County?Will improved quality of neonatal care lead to an increase in utilization of new born care services in Bungoma County?Does improved information flow amongst health practitioners result in better services for neonates in Bungoma County?

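### The 125 + 125 neonates for clinical observation are sized on a change in facility presentation that a sample of babies already at a facility cannot show

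*Protocol article*

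**What the plan says.** The sample appears in the Protocol article under *Selection of participants for the clinical observations of neonatal services*. Its basis is given as "The sample size calculation is based on net change in the proportion of neonates who present with complications in health facilities". The paragraph explains that "a significant proportion of babies born with complications are missed out or only a few of them present to health facilities", puts the present level at 21% ("In Bungoma County, currently only 21% present in health facilities"), and aims for a 50% relative rise, to 32%. It continues: "Given that births are 29,845 [16] and current situation is 21% presenting in health facilities we get a population of 6268 neonates". From there it states 125 neonates for the intervention group and 125 for the control group. Questionnaires are to be given among the selected cases, and the reader is referred to Additional file 2.

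What observation is for is stated elsewhere. Under *Control group – Minimizing bias and contamination*: "Quality of care will be determined through observations of service provision by clinicians". The list of qualitative tools gives the same purpose for observing neonatal care. Utilisation has its own sources in the *Control group* section: abstraction forms in all nine facilities throughout the project, and reports from community health workers and volunteers on the cases they refer, including those who do not arrive.

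**The concern.** A sample size should be justified by a quantity that the sample can estimate. The share of complicated newborns who reach a facility needs a denominator that includes those who do not reach one. A sample for observing care in hospitals, from a population built by multiplying births by the presenting share, holds only the numerator. A larger sample of the same kind would not help.

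At stake is the meaning of 125 per group. A reader would take it as evidence that the observation component can answer its question. No quality-of-care proportion, expected difference or margin of error is given for it, so its size has not been checked against the result the observations will produce.

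**Working it through.** **Inputs from the protocol.** Births 29,845; baseline share presenting 0.21; target 0.32 (an exact 50% rise is 0.21 × 1.5 = 0.315); 125 neonates per group; five intervention and four control hospitals. Alpha and power are not stated for this sample.

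**Step 1: the source population.** 29,845 × 0.21 = 6267.45, which rounds up to the stated 6268. The frame is therefore the babies who present. The 21% is described for babies with complications but applied to all births. That inconsistency does not affect this point: on either denominator, the product counts presenters.

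**Step 2: the sizing quantity within that frame.** Among babies drawn from presenters, the proportion presenting is 1 in the intervention group and 1 in the control group, whatever the true rates in the county. The difference is 0 by construction, so 0.21 against 0.32 cannot be estimated.

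**Step 3: an alternative reading.** Taken alone, the opening sentence could mean the share of facility neonates who have complications, which a facility sample could estimate. The sentences after it rule this out. They contrast babies who present with babies who are missed, and they use the 21% to build the frame.

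**Step 4: does 125 follow from 21% to 32%?** With an assumed two-sided 5% level and 80% power (pooled variance under the null), n per group is

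(1.96 × √(2 × 0.265 × 0.735) + 0.8416 × √(0.21 × 0.79 + 0.32 × 0.68))² / 0.11² ≈ 252.

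The stated 125 is not reproduced. No two-group variant tried at 80% or 90% power gave it. Some unconventional routes come close, such as a precision formula at 21% with a 7-point margin (125 to 127). This step is background only, since Step 2 holds at any sample size.

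**Step 5: what 125 per group gives for a quality-of-care proportion.** Assume 50%, the least favourable value.

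- One group, simple random sampling: 1.96 × √(0.25/125) = 8.8 points.
- Difference, simple random sampling: 1.96 × √(2 × 0.25/125) = 12.4 points.

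**Step 6: clustering by hospital.** Assume equal spread, so 125/5 = 25 neonates per intervention hospital and 125/4 = 31.25 per control hospital. The design effect is 1 + (m − 1) × ICC.

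| Assumed ICC | Design effect, intervention | Design effect, control | 95% half-width of the difference |
|---|---|---|---|
| 0 | 1 | 1 | 1.96 × √(0.002 × 2) = 12.4 points |
| 0.01 | 1.24 | 1.3025 | 1.96 × √(0.002 × 2.5425) = 14.0 points |
| 0.05 | 2.20 | 2.5125 | 1.96 × √(0.002 × 4.7125) = 19.0 points |

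Here 0.002 = 0.25/125. The ICC values are assumptions; the protocol gives none.

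**The case against.** The strongest reply is that the mismatch does little damage. The protocol does not say that presentation will be estimated from these 250 babies. Utilisation is assigned to facility abstraction and community reports, which include non-arrivals. The primary outcome is deaths at the nine facilities. The five secondary outcomes rest on sampled mothers, call-centre contacts, health workers and unit admissions, and none is explicitly defined on this sample. This stands, and it limits the point. A reader might infer that the utilisation questions are left without data; the *Control group* section shows otherwise.

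A second reply is that the sample is linked to the quality-of-care observations only by its section heading, that questionnaires are also planned, and that Additional file 2 is not shown. It is fair that the sample may have further uses. But any questionnaire among the selected cases is still confined to babies who presented. No alpha, power or formula in the additional file could make presentation estimable among presenters.

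A third reply concerns the remedy. The protocol's adherence outcome counts health workers, not neonates, so a per-neonate proportion has to be defined before a precision can be attached to it. The utilisation data also miss sick newborns who are neither referred nor attend, so they do not give a complete denominator for presentation. Both objections are right, and the fix allows for them.

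A reader might also infer from Step 4 that the sample is underpowered, or that a requirement of about 250 per group was halved. The document does not establish this: alpha and power are not stated, and other routes come near 125.

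**Conclusion.** The stated basis for the observation sample is wrong as written. Its target (a rise in the share presenting), its frame (those who present) and its purpose (observing care) do not fit together. The 250 neonates give no information on 21% against 32%, and this follows from the protocol's own figures without any assumption.

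The consequence is limited to one ancillary sample. The mortality outcome is unaffected, no listed secondary outcome is explicitly defined on these babies, and the presentation question has its own data. It should be corrected, but the study's main conclusions do not depend on it.

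The practical size of the issue is the precision the sample can offer for quality of care: ±12.4 points on a difference at best, and about ±14 to ±19 with clustering. These figures assume a proportion of 50%, equal numbers per hospital and ICCs of 0.01 to 0.05.

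**What to change.** In *Selection of participants for the clinical observations of neonatal services*:

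1. Remove the 21% to 32% change as the basis for this sample.
2. Define a quality-of-care proportion with observed neonates as the denominator, and state that 125 per group is the size for it. Give the precision at an assumed 50%: ±8.8 points per group and ±12.4 on the difference under simple random sampling, widening to about ±14 and ±19 on the difference at assumed ICCs of 0.01 and 0.05.
3. State that change in presentation is assessed from the utilisation data described under *Control group – Minimizing bias and contamination*, not from this sample, and that newborns neither referred nor attending are missed there.
4. If a presentation proportion is reported, label it as added after study start. The abstract says that the study has commenced, and registration was retrospective.

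The cost is protocol wording and the work of defining the proportion. No further neonates are needed. The downside is a less favourable stated precision.

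### The 125-per-group clinical-observation sample does not follow from the 21% to 32% target given as its basis, and babies already in facilities cannot measure that target

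*Protocol article*

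**What the plan says.** In the section on selecting participants for clinical observations, the protocol article gives the basis of the calculation: "The sample size calculation is based on net change in the proportion of neonates who present with complications in health facilities". The starting value is "In Bungoma County, currently only 21% present in health facilities", and the aim is "we seek to increase this by 50%, (21 to 32" (both figures are percentages). Annual births of 29,845 are then combined with the 21%: "current situation is 21% presenting in health facilities we get a population of 6268 neonates". The next sentence draws the conclusion: "This means we get a sample size of 125 neonates for intervention and 125 for control group". The section gives no significance level, power, margin of error or formula, and points to Additional file 2, which is not shown.

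Three other places bear on this. The section on community members gives a one-proportion formula with a finite-population correction for the mothers' survey: "The study will allow a margin of error of 5% at confidence level of 95" per cent. The section on hospitals fixes the sites: "Five Facilities will be intervention sites while four health facilities will be the control sites". The section on the control group, bias and contamination plans to measure utilization separately, by data abstraction in the nine facilities and from community health worker referrals, including referred cases that never arrive.

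**The concern.** The text reads as a derivation: a target change, a population, and a sample size that is said to result. A reader will take it that 125 per group is enough to detect the planned 50% relative increase in presentation. Two things stand in the way. The number is far below what a two-group comparison of 21% with 32% usually requires. And the babies sampled are those available for observation of care, so all of them have the characteristic whose frequency is to be measured. Increased access and utilization is the first project outcome in Table 1, so a claim that the study is sized for it would carry weight with readers.

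**Working it through.** **Inputs.** From the section on clinical observations: p1 = 0.21, p2 = 0.32 (an exact 50% increase is 0.21 × 1.5 = 0.315), 125 per group, 29,845 births. Not stated there and therefore assumed: significance level, sidedness and power. I take two-sided 5% and 80% power and show the range.

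**The plan's own intermediate figure.** 29,845 × 0.21 = 6267.45, which the plan gives as 6268. The product is reproduced. By construction it counts neonates who present.

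**Sample size for 21% against 32%.** Unpooled formula: n = (z_α + z_β)² × [p1(1−p1) + p2(1−p2)] / (p2−p1)².
- p1(1−p1) + p2(1−p2) = 0.1659 + 0.2176 = 0.3835; (p2−p1)² = 0.0121.
- Two-sided 5%, 80% power: (1.960 + 0.842)² = 7.849, so n = 7.849 × 0.3835 / 0.0121 = 248.8.

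| Assumption | Unpooled | Pooled variance |
|---|---|---|
| One-sided 5%, 80% power | 196.0 | 198.0 |
| Two-sided 5%, 80% power | 248.8 | 251.5 |
| Two-sided 5%, 90% power | 333.0 | 336.2 |
| Two-sided 5%, 50% power | 121.8 | 123.7 |

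With 31.5% in place of 32%, two-sided 5% and 80% power needs 271.7 (unpooled) or 274.5 (pooled). Even one-sided 10% with 80% power needs about 143 to 144 for 32%. All figures are per group and make no allowance for correlation within the nine hospitals, which would raise them.

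**What 125 corresponds to.** Standard error of the difference = √(0.3835/125) = 0.0554, and 0.11/0.0554 = 1.986. Power is Φ(1.986 − 1.960), about 51%; with the pooled variance in the test it is 50.4%. For 31.5% it is about 47%. These figures show only that the number does not match the stated change. They do not describe a test that this sample could perform.

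**Another route to 125.** The formula for the mothers' survey is x = z² r(100−r), n = Nx / [(N−1)E² + x].
- Check: N = 29,845/2 = 14,922.5, r = 50, E = 5 gives x = 9604 and n = 374.5, the plan's 375.
- Same formula with N = 6268/2 = 3134, r = 21, E = 7 gives x = 6373.2 and n = 3134 × 6373.2 / (3133 × 49 + 6373.2) = 124.9.
- With r = 32 and E = 8 it gives 125.4.

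The 7- and 8-point margins are assumptions; the section states none. A requirement of about 250 per group treated as a total and halved would also give about 125. The source of the figure cannot be established from the text.

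**Can the sample measure the target?** The proportion presenting needs a denominator that includes babies who did not present. The section is about observing care, and the population it derives is obtained by multiplying by the share presenting. Every sampled neonate is therefore in the numerator, and the observed proportion is 100% by construction in both groups at any sample size.

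**Denominator of the 21%.** The opening sentence can be read as a share of all neonates (those who present with complications). The next sentence speaks of babies born with complications, few of whom reach a facility. On the first reading, 29,845 × 21% is the number presenting with complications. On the second, the 21% should multiply the number of babies with complications, which is not given, and 6268 is wrong.

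**The case against.** The strongest reply is that 125 was never a power calculation. The mothers' survey is sized by precision in a halved population, and the same method with an assumed 7-point margin gives 125 here. That would also explain why a population of 6268 was derived at all, since a power calculation does not need one. This stands as a possibility, so a reader should not infer that a power calculation was wrongly executed or a total wrongly halved; the text shows neither. But a margin-of-error calculation is not a calculation for a net change, which is the basis the section states.

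Second, about 250 per group depends on a significance level and power that the section does not give, and Additional file 2 is not shown. That is correct, and the figure must carry its assumptions and range. No setting in that range comes near 125.

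Third, nothing in the article says that 21% against 32% will be tested in these 125 neonates. Utilization is measured separately, and presentation is neither the primary outcome nor one of the five secondary outcomes. This stands, and it limits the consequence. It is tempting to conclude that the study will run an underpowered test and report an uninformative null result; the article does not support that, because this sample cannot yield such a test and none is planned in it.

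Fourth, the 6268 is a definite error only on one of two readings of the 21%. This stands too: the text is ambiguous, and what is needed is a stated denominator.

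**Conclusion.** The point holds as a mismatch between a stated sample size and its stated justification. The conclusion that needs no assumption about error rates is that neonates selected for observation in facilities carry no information on the proportion presenting. The numerical conclusion rests on an assumed significance level and power and ignores clustering: about 250 per group at two-sided 5% and 80% power, with a range of about 196 to 336, against a stated 125 that matches about 50% power. How 125 was reached is unknown, and the 6268 is unclear rather than shown to be wrong. This should be fixed but does not threaten the trial's listed outcomes.

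**What to change.** Keep 125 per group and change the text as follows.

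- Remove the 21% to 32% change as the justification for this sample, and attach no power statement for that contrast to it.
- State the purpose as observation of quality of care, and give the precision: 1.96 × √(0.25/125) = 0.088, about ±8.8 percentage points per group for a proportion near 50%, before allowance for clustering in five and four hospitals.
- State whether the 21% is a share of all births or of babies born with complications, and correct or remove the 6268 accordingly.
- Say that change in presentation will be assessed from the nine-facility data abstraction and the community health worker referral records, including cases that fail to arrive. Note the limits: these sources cover only identified or referred cases, ascertainment may change with the intervention, and the result is not directly comparable with the 21% from the county HMIS.

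The cost is a text correction with no extra participants or data collection. The downside is that the study can no longer claim that this sample is sized to detect the 50% increase in presentation.

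### The 125 neonates per group for the clinical observations does not follow from the stated change of 21% to 32%; at two-sided 5% it gives about 51% power for that change, before clustering.

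*Protocol article*

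**What the plan says.** The point concerns the protocol article, Sample size determination, under Selection of participants for the clinical observations of neonatal services.

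- Basis: "The sample size calculation is based on net change in the proportion of neonates who present with complications in health facilities".
- Starting level: "In Bungoma County, currently only 21% present in health facilities".
- Target: "we seek to increase this by 50%, (21 to 32" (both figures are percentages).
- Population: "current situation is 21% presenting in health facilities we get a population of 6268 neonates".
- Result: "This means we get a sample size of 125 neonates for intervention and 125 for control group".

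The section prints no significance level, power, test or formula. It refers to Additional file 2, which is not at hand. The only confidence level in the article belongs to the separate survey of mothers (Selection of community members): "The study will allow a margin of error of 5% at confidence level of 95" per cent.

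The groups are made up of whole hospitals: "Five Facilities will be intervention sites while four health facilities will be the control sites" (Selection of hospitals for the study).

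**The concern.** The wording presents 125 per group as the consequence of a baseline, a target and two groups. A reader will take it that the sample was sized to detect a rise from 21% to 32% against a control group with ordinary power. If the figure does not follow from those inputs, the article credits this part of the study with a sensitivity it lacks.

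The complaint is not that detail was left out; an article may leave its formula to a supplement. It is that a printed number does not follow from the printed inputs under any usual choice of the unprinted ones.

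**Working it through.** **Inputs.** From the article: p1 = 0.21; p2 = 0.32 (an exact 50% rise is 0.21 × 1.5 = 0.315); 125 per group; population 29,845 × 0.21 = 6267.45, printed as 6268. Assumed, because not printed for this step: two-sided 5% (the 95% level of the mothers' survey carried over) and 80% power, with one-sided 5% and 90% power as the range.

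**1. The article's other sample size does reproduce.** For the mothers' survey, x = 1.96² × 0.5 × 0.5 = 0.9604 and N = 29,845 / 2 = 14,922.5. Then n = N x / ((N − 1) × 0.05² + x) = 374.5, matching the printed 375. Applied here with r = 0.21 and N = 6268, the same formula has x = 1.96² × 0.1659 = 0.6373 and gives n = 245.0. That is not 125.

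**2. Two-group requirement, 21% v 32%.**
n per group = (z_α + z_β)² × [p1(1 − p1) + p2(1 − p2)] / (p2 − p1)²
= (1.960 + 0.8416)² × (0.1659 + 0.2176) / 0.11²
= 248.8. The pooled-variance form gives 251.5.

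| Setting | Needed per group |
|---|---|
| Two-sided 5%, 80% power, 32% | 249 to 252 |
| Two-sided 5%, 80% power, 31.5% | 272 to 275 |
| Two-sided 5%, 90% power, 32% | about 333 to 337 |
| One-sided 5%, 80% power, 32% | 196 to 198 |

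Against the first row, 125 / 248.8 = 0.50. Against the most lenient row, 125 / 196 = 0.64.

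**3. What 125 per group delivers (two-sided 5%).**
- SE = √(0.3835 / 125) = 0.0554, and 0.11 / 0.0554 = 1.986. Power = Φ(1.986 − 1.960) = 51.0% (50.4% pooled).
- With 31.5% as target: SE = 0.0553, and 0.105 / 0.0553 = 1.900. Power = 47.6% (47.1% pooled).
- One-sided 5%, 32%: about 63%.
- 95% half-width of the difference: 1.96 × 0.0554 = 10.9 points, against the 11 points sought.
- 80% power is reached only for 21% against 36.8%.

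**4. If net change means a before-after difference between groups.** Assume 125 separate neonates per group at each of two times, with 21% in three cells and 32% in the fourth. The variance is (3 × 0.1659 + 0.2176) / 125 = 0.00572, so SE = 0.0756 and power is about 31%. About 464 per cell would be needed for 80%. The article does not describe this layout, so these figures only show the direction.

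**5. Clustering.** All the figures above treat neonates as independent. As an illustration, 125 / 4.5 ≈ 28 neonates per hospital and an assumed intracluster correlation of 0.01 give a design effect of 1 + 26.8 × 0.01 = 1.27, and power of about 42%. The article gives no such correlation.

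**6. Where 125 might come from.** Several routes land near it:
- half of 248.8 is 124.4, which would mean taking the per-group number as the total;
- half of 245.0 is 122.5;
- 2% of 6268 is 125.4;
- a one-sample test of 31.5% against a fixed 21% gives 128.3, or 125.7 after a finite-population correction with N = 6268.

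None is a two-group comparison with conventional power.

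**The case against.** **A one-sample calculation may have been meant.** The target is worded as a rise from the present level, 6268 is quoted just before the result, and the corrected one-sample figure of 125.7 uses both and is within one of the printed number. This may well be the origin. It does not support the sentence as written, because a net change and a control group of equal size describe a comparison of groups, not a test against a fixed value.

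**Significance level and power are not printed.** This stands in part. A reader might infer that 125 is simply half of what is needed; that holds only for 80% power at two-sided 5%. The 51% needs only the two-sided 5% level. The shortfall itself depends on neither choice: every two-group variant tried at 80% to 90% power needs at least 196.

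**The sample could never test 21% against 32%.** This also stands. The 6268 are neonates who already present, and a sample of presenters cannot estimate the proportion who present. Under Control group – Minimizing bias and contamination, utilization is measured by record abstraction in all nine facilities and by referral information from community health workers. A reader might infer that a null result from these 250 neonates would be mistaken for no effect on presentation. The article does not support that, because this sample would not supply the test.

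**No declared outcome is sized by this figure.** Correct. The primary outcome is the reduction in newborn deaths, and the proportion presenting is not among the five secondary outcomes. A reader might infer that the trial's main comparison is underpowered; nothing here shows that.

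**Conclusion.** The point holds, at moderate severity. The printed 125 per group does not follow from a net change of 21% to 32% between two groups. The requirement is about 249 to 252 per group at two-sided 5% and 80% power, and at least 196 under the most lenient setting tried. As printed, 125 per group gives roughly an even chance of detecting the full target difference, and a margin as wide as that difference. Clustering, or a before-after contrast between groups, would lower the power further.

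This rests on reading the sentence as a comparison of intervention with control, and on two-sided 5% for the 51%. How 125 was reached cannot be established from the article. The consequence is limited to the description of the clinical-observation component.

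**What to change.** In Selection of participants for the clinical observations of neonatal services:

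1. Remove the statement that 125 per group follows from 21% to 32%, and name the comparison meant (two groups after the intervention, or a before-after difference between groups).
2. Then do one of the following:
   - keep 125 per group and say what it delivers at two-sided 5%: about 51% power for 21% v 32%, 80% power only from 21% to about 37%, and a margin of about 11 points on the difference, all before clustering; or
   - state that 21% v 32% needs about 250 per group at two-sided 5% and 80% power, before an allowance for clustering in nine hospitals. The figure of 250 should not be presented as sufficient in itself.
3. State that the 21% to 32% change will be assessed from the facility abstraction and community referral data, and that the 125 + 125 serve the clinical observations.

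The first option costs wording only and needs no further neonates, though the stated performance becomes less favourable. The second doubles the sample from 250 to about 500 in total before the clustering allowance.
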